### Data management

Data is entered directly into electronic case report forms (eCRF) by research teams at the site using MACRO v4 database software. Delegated staff who have undertaken training to use the software and submitted their current curriculum vitae (signed and dated) and GCP certificate (dated in the last 3 years) will be given access to log in.

Site staff are expected to input data directly into the eCRF within the clinical environment and in real time. MACRO v4 has been programmed to calculate the rate of wound drainage (millilitres per hour). If the rate falls below 1.25 ml/h, MACRO v4 will recommend removal of the drain in keeping with the protocol. This process will only work if data is entered in real time.

Electronic versions of the patient-reported questionnaires will be stored on the LCTU’s portal. Research staff at the site will have individual logins to access this documentation. It is expected that sites will download the questionnaires and hand them to patients for completion at specific time points as stipulated in the protocol. It is also expected that the responses will be transcribed to the eCRF on the same day as the patient completes them.

To ensure the database is only updated or amended by authorised individuals, the data entry system requires users to have a username and password, to be entered at the start of each data entry session.

Users should log out of the data entry system each time they leave their work station unattended. Each computer station should be set to revert to a password-protected screen saver mode when left idle for 10 min.

Individuals should only work under their own username and should not log anyone else onto the system. The MACRO database package has several methods built in to maximise security:
Each password must contain between 6 and 15 characters, including lower and upper case letters and at least 1 number.If left idle for 20 min MACRO automatically locks out the user, who must then re-enter their password to regain access to the database.

MACRO records any changes made to data in the system, and all user activity is logged. For a particular question, the audit trails consist of a chronological record of the status, response value, warning messages and overrule reasons, reasons for change, comments and lock status.

Whenever any of these items are changed, a record is kept of the date and time, and the username of whoever made the change. Users with appropriate permission have access to view audit trails; however, no-one is able to change or delete an audit trail. The audit trail allows the LCTU to monitor the quality of individual team members’ data input and highlight training needs if consistent errors are found.

### Statistical methods

The primary analysis will be carried out on the full data set and will be based on the intention to treat principle, retaining patients in their initially randomised groups irrespective of any protocol violations.

Missing data are expected to be limited, and final analyses are planned to be carried out on a complete case basis. If substantial missing data (> 10%) are observed in either a study outcome or key prognostic covariate, then multiple imputation using chained equations will be applied.

There are no formal comparisons of treatment groups, and therefore, no levels of significance against which hypotheses will be tested. As a guide however, all results will be reported using nominal 95% confidence intervals.

As this is an external pilot study, all data analyses shall take the form of descriptive statistics. Continuous data shall be summarised as medians with associated inter-quartile ranges and categorical data shall be summarised as frequencies of counts and associated percentages.

In terms of clinical outcomes, aside from descriptive statistics, informal comparisons between allocated groups will be made using the difference in means for continuous covariates and differences in rates for categorical covariates.

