### NDII

The NDII is a procedure-specific health-related quality of life (HRQoL) assessment tool. The tool is validated for use in patients who have undergone selective or modified radical neck dissection [20]. Patients will undertake a baseline NDII pre-operatively and at follow-up visit 2 (4–6 weeks). Although the NDII is not validated for use 4–6 weeks after surgery, there is evidence that the NDII score at this early juncture is representative of longer-term HRQoL [23].

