### Allocation

Randomisation lists will be computer-generated by the statistician prior to the recruitment of the first patient. Patients will be randomised using a 1:1 ratio. Lists will be produced based on the principle of randomly permuted blocks with random block sizes of 2 and 4. Patients will only be stratified according to the hospital in which they receive their treatment.

The process of randomisation will be undertaken pre-operatively using the “Treatment Allocation RanDomIsation System” (TARDIS) software version 3.8. This software has been developed by the LCTU. The allocation will be concealed to everyone including the person performing the randomisation. Once randomisation has been performed, the surgeon caring for the patient will receive an automated email which contains a link to reveal the allocation. Once the patient has undergone their neck dissection immediately prior to the point of wound closure, the surgeon will open the link and login to TARDIS to reveal the allocation. The exact time and date this occurs will be recorded and cross-referenced against the start and finish times of surgery as a quality assurance step to minimise performance bias. The randomisation process can be performed either centrally or at the site once the eligibility criteria have been entered and signed off by the Principal Investigator.

As part of the blinding strategy, any clinicians who will be assessing study outcomes must leave theatre prior to the revealing of treatment allocation. They must not return until the theatre has been cleared of any evidence of FS usage. The surgeon administering the FS will not be allowed to assess study outcomes for the patient and must delegate this responsibility to a suitable colleague.

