### Complexity of the intervention

One of the differences between surgical trials and pharmacological trials is the complexity of the intervention. Surgical interventions are multi-faceted and depend on the performance of the wider healthcare team in addition to the skill, experience and decision making of the operating surgeon. Outcomes in the DEFeND study are dependent on the perioperative management of patients; the neck dissection surgery itself; the need for other synchronous surgical procedures e.g. resection of the primary tumour; and the intervention itself. As the administration of FS is considered SOC, it is expected that randomisation will balance the variables equally across both arms.

In order that surgeons administer FS in a standardised way, a video has been produced and laminated sheets hung up in operating theatres providing temporal detail of the protocol. Many surgeons will be experienced at administering FS, but for those that are not ‘ad hoc’, training will be available. It is recognised that surgeon level performance will vary and as such the ideal standard procedure will not be replicated on each occasion. Currently, there are no requirements for surgeons to perform the surgery/administer FS a minimum number of times or achieve a predetermined standard. This is primarily to reflect the ‘real-world’ nature of the study. If the impact of the learning curve is clearly demonstrated in the pilot data, then surgeons acquiring a certain level of expertise to participate in the phase III trial will be considered.

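### Continuous outcomes get only median/IQR and raw mean differences; adding the SD, the baseline/follow-up correlation and baseline-adjusted NDII and pain estimates would inform phase III better at no data cost

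*Protocol article*

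**What the plan says.** All of this is in the protocol article.

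- **Statistical methods, summary:** "Continuous data shall be summarised as medians with associated inter-quartile ranges". Categorical data are given as counts and percentages. No mean, SD or correlation is named.
- **Statistical methods, comparison:** for clinical outcomes, "informal comparisons between allocated groups will be made using the difference in means for continuous covariates and differences in rates for categorical covariates". In addition, "all results will be reported using nominal 95% confidence intervals".
- **Statistical methods, status:** "There are no formal comparisons of treatment groups, and therefore, no levels of significance against which hypotheses will be tested".
- **Allocation:** "Patients will be randomised using a 1:1 ratio", and "Patients will only be stratified according to the hospital in which they receive their treatment".
- **NDII and Table 1:** NDII is completed before surgery and again at follow-up 2. Neck pain VAS is recorded at baseline, daily in hospital and at each follow-up.
- **Objectives and Sample size:** informing the phase III sample size is a key objective and one of the two main outcomes of interest. The clinical outcome singled out is the surgical complication rate.
- **Outcomes:** the candidates for phase III also include continuous measures: drainage volumes, times to drain removal and to discharge, NDII and pain.

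**The concern.** The article fixes a summary (median and IQR) that differs from the quantity compared (the mean), and it names neither measure of spread nor measure of association that a continuous phase III endpoint would need. Sizing a trial on a mean difference needs an SD. Sizing it on a baseline-adjusted analysis also needs the baseline/follow-up correlation. A pilot that measures NDII and pain at both times can supply both.

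The comparison is also stated as a plain difference although allocation is stratified by hospital and baseline values of two outcomes are in hand. At stake is precision in the pilot's descriptive intervals, and how directly the pilot serves one of its own objectives if phase III uses a continuous endpoint.

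**Working it through.** **1. The plan's own figures.** The Sample size section gives precision for proportions only. With SE = √(p(1 − p)/n) and n = 50:
- p = 0.30: SE = √(0.21/50) = 6.48%, CI 17.3% to 42.7% (stated 6.5%, 17–43%).
- p = 0.50: SE = √(0.25/50) = 7.07%, CI 0.361 to 0.639 (stated 0.36 to 0.64).

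Both reproduce with all 50 patients as the denominator. There is no corresponding figure for a continuous outcome, and no SD, correlation or target difference is given. Everything below is therefore in SD units or rests on stated assumptions.

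**2. Precision of the pilot's NDII and pain differences.** Inputs: 25 per arm (Sample size); r assumed. Half-width in SD units = 1.96 × √[(2/25)(1 − r²)].

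| r (assumed) | 1 − r² | 95% half-width |
|---|---|---|
| 0 (raw) | 1.00 | 0.55 SD |
| 0.3 | 0.91 | 0.53 SD |
| 0.5 | 0.75 | 0.48 SD |
| 0.7 | 0.51 | 0.40 SD |

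**3. What r would mean for phase III.** Assume two-sided 5%, 80% power, 1:1 allocation and standardised difference d. Then n per arm = 2(1.96 + 0.84)²(1 − r²)/d².

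| d | r = 0 | 0.3 | 0.5 | 0.7 |
|---|---|---|---|---|
| 0.5 | 63 | 58 | 48 | 33 |
| 0.3 | 175 | 159 | 131 | 89 |

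This applies only if phase III uses a baseline-adjusted continuous endpoint.

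**4. What the stated summaries give.**
- *SD from the interval.* A t-interval for a mean difference at 25 per arm has half-width t(0.975, 48 df) × SD × √(2/25) = 0.57 × SD. The pooled SD is therefore the half-width divided by 0.57, for a complete-case, equal-variance interval. If the multiple imputation planned for more than 10% missing data is used, the interval also carries between-imputation variance and this step is no longer exact.
- *SD from the IQR.* IQR/1.349 equals the SD under normality. Under assumed log-normal shapes with log-SD 0.5, 0.75 and 1.0 it gives 84%, 68% and 50% of the true SD. A sample size built on it would be too small by 1/0.84² = 1.4, 1/0.68² = 2.2 and 1/0.50² = 4.0 times.
- *Correlation.* It cannot be derived from medians, IQRs or between-arm intervals.

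**5. How well the pilot can estimate these.** On 48 df the 95% limits for an SD are 0.83 and 1.25 times the estimate, so n scales by 0.70 to 1.56 (the squares, from unrounded factors). The one-sided 80% upper limit is 1.10 × SD. For r = 0.5 on 50 patients, Fisher's z is 0.549 ± 1.96/√47 = 0.549 ± 0.286, so r lies between about 0.26 and 0.68. Both quantities need an interval.

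**6. Complications.** Hospital adjustment gains little. With two equal sites at assumed rates of 15% and 25%, site explains 0.05²/(0.20 × 0.80) = 1.6% of the variance.

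**The case against.** The strongest reply is that this is a 50-patient pilot whose comparisons are expressly informal, untested and descriptive, reported in an article that condenses a fuller protocol. Covariate adjustment and table contents often sit in an analysis plan, so silence is not exclusion. Randomisation keeps a raw difference unbiased. Median/IQR is a sensible summary for volumes and times, and the mean comparison is offered in addition to it, so the two are not contradictory. The complication rate needs event proportions, which are reported.

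All of that stands, and it rules out several stronger readings that a reader might infer:

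- *That phase III would have to be sized from an IQR.* The team holds patient-level data and can compute any SD or correlation. The SD also follows from the interval for a mean difference.
- *That leaving out previous neck treatment exposes the comparison to a factor that by itself raises risk to 40%.* The Background attaches that figure to previous chemo-radiotherapy or to older patients with co-morbidities or polypharmacy, so it is a composite. Even with an assumed 25% prevalence and risks of 40% v 15%, the average risk is 21.25%. The raw half-width is 1.96 × √(0.2125 × 0.7875 × 2/25) = 22.7 points. Prior treatment explains 0.25 × 0.75 × 0.25²/0.1673 = 7% of the variance, so adjustment gives about 22.7 × √0.93 = 21.9 points, a gain of under 1 point.
- *That the unadjusted analysis relies on the remark under Complexity of the intervention that* "it is expected that randomisation will balance the variables equally across both arms". That remark concerns perioperative care, surgery, synchronous procedures and the intervention. The Statistical methods section does not appeal to it.

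The reply does not remove the remaining point. The article states a summary and a comparison outright, and a better version of each is available from data already being collected.

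**Conclusion.** The point holds as a cost-free improvement, not as an error that undermines the pilot. As stated, the NDII and pain comparisons forgo whatever precision baseline adjustment offers: nothing at r = 0, a half-width falling from 0.55 to 0.48 SD at r = 0.5, and to 0.40 SD at r = 0.7. These r values are assumptions. The named summaries give the SD only indirectly and omit the baseline/follow-up correlation, which can move a continuous-endpoint phase III from 63 to 33 per arm over the assumed range (d = 0.5, 80% power).

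The consequence is limited to continuous endpoints. Sizing on the complication rate is not affected by the missing SD or correlation, and the documents do not support a claim of bias or invalid inference.

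**What to change.** In Statistical methods, or in the analysis plan if that is where the detail sits:

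1. For continuous outcomes, report mean and SD beside median/IQR, with a confidence limit for the SD (for example the one-sided 80% upper limit, 1.10 × SD on 48 df).
2. For NDII and pain VAS, report the baseline/follow-up correlation with its interval.
3. Estimate the NDII and pain differences from a linear model with arm, hospital and baseline value. Present them as descriptive estimates with 95% CIs and no test.
4. Optionally, add a hospital-stratified (Mantel-Haenszel) risk difference for complications, which matches the randomisation although the expected gain is small.

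The cost is a few lines of text and some extra table columns. No new data, visits or patients are needed, and the analysis stays descriptive.

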### Data monitoring

Formal interim analyses of the accumulating data will be performed at 6 monthly intervals after the recruitment of the first patient. A formal Independent Data Monitoring and Safety Committee (IDMSC) will not be convened. In keeping with the guidance outlined in the document ‘Guideline in Data Monitoring Committees’ published by the Committee for Medicinal Products for Human Use [25], it is thought that an IDMSC is not required. This is because patients will be treated for a very short period of time (single administration during surgery) and fibrin sealants are well characterised and already widely used within healthcare. Although there are potential risks to patients, these are incredibly rare and known.

The independent members of the TSC (chairperson, expert, statistician) will take responsibility for reviewing all interim safety data. The independent members will be asked to give advice on whether the accumulated data from the trial, together with results from other relevant trials, justifies continuing recruitment of further patients or further follow-up. Given this is a pilot/feasibility study, it is anticipated that the TSC will only recommend termination on grounds of safety.

### Safety

Surgical complications and adverse reactions to fibrin sealant that are Clavien-Dindo grade IV or above (see Tables 2 and 3) will be the only events reported to assess safety. As the ‘Clavien-Dindo Classification of Surgical Complications’ constitutes a primary outcome measure for the DEFeND pilot trial, the presence of post-operative complications along with their grade will be recorded on the eCRF. All complications related to the neck dissection surgery and/or use of fibrin sealant that are Clavien-Dindo grade III-b or below that meet the definition of serious are exempt from Serious Adverse Event (SAE) reporting. Such events are ‘expected’ and should only be recorded in the relevant section of the eCRF.

Post-operative complications related to either neck dissection or use of fibrin sealant that are Clavien-Dindo grade IV or above are ‘unexpected’ for the DEFeND trial. The LCTU will notify the main REC of all Suspected Unexpected Serious Adverse Reactions (SUSARs) occurring during the study according to the following timelines; fatal and life-threatening within 7 days of notification and non-life-threatening within 15 days. All investigators will be informed of all SUSARs occurring throughout the study.

Site staff (with the exception of the surgical team) will be blinded; therefore, the SAE reporting form will not state which arm the patient has been randomised to. For the purposes of SAE reporting, it should be assumed that the patient was randomised to receive fibrin sealant (i.e. interventional arm). Causality should be assigned to the following:
AnaestheticGenerality of surgery (including surgical airway, primary tumour resection)Neck dissection surgeryUse of fibrin sealant

Pregnancy is listed as an exclusion criterion for entry to the DEFeND trial. In the event of a patient becoming pregnant after recruitment to the trial, this fact should be reported in the same way as an SAE. The guiding principles in this event are as follows:
If the patient has not yet received treatment, or completed treatment, the patient may be withdrawn from the trial.Once treatment is complete, i.e. the patient is in follow-up phase, it may well be possible to retain the patient to the conclusion of the trial.A decision will be made in the best interests of the patient between the treating clinician and the Chief Investigator as to retention in the trial and any continuing cancer therapy.

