	Collection deep to platysma requiring drainage (not under GA)	**IIIa**
	Collection deep to platysma requiring drainage (under GA)	**IIIb**
	Large collection with organ and/or life-threatening sequelae (i.e. airway obstruction, severe sepsis, septic shock)	**IV** (**a** or **b** depending on organ dysfunction)
Other surgical site infection	Localised infection requiring topical or non-invasive treatment	**I**
	Infection requiring treatment with antibiotics only	**II**
	Collection requiring drainage (not under GA)	**IIIa**
	Collection requiring drainage (under GA)	**IIIb**
	Large collection with organ and/or life-threatening sequelae (i.e. airway obstruction, severe sepsis, septic shock)	**IV** (**a** or **b** depending on organ dysfunction
Bleeding/haematoma	Haematoma not requiring drainage or suitable for simple aspiration with a needle (not radiologically guided)	**I**
	Need for blood transfusion	**II**
	Requiring drainage (not under GA). Includes radiologically guided aspiration/drainage	**IIIa**
	Requiring drainage or return to theatre for haemostasis (under GA)	**IIIb**
	Haematoma/haemorrhage sufficiently large to obstruct airway or cause hypovolaemic shock	**IV** (**a** or **b** depending on organ dysfunction)
Chyle leak	Low output leak (< 500 ml/24 h) suitable for low-fat diet and compression only	**I**
	Requirement for pharmacological management including total parenteral nutrition	**II**
	Radiologically guided occlusion	**IIIa**
	Return to theatre for the procedure under GA	**IIIb**
	Evidence of end-organ dysfunction	**IV** (**a** or **b** depending on organ dysfunction)
Wound breakdown	Superficial skin dehiscence (platysma layer intact) managed with dressings	**I**
	Small fistula managed by an enteral tube or parenteral nutrition only	**II**
	Deep dehiscence (through platysma layer) or fistula managed with procedure not under GA	**IIIa**
	Deep dehiscence (through platysma layer) or fistula managed with the procedure under GA	**IIIb**
	Evidence of end-organ dysfunction	**IV** (**a** or **b** depending on organ dysfunction)
Seroma/sialocele	Small collection not requiring drainage or suitable for aspiration with a needle (not radiologically guided)	**I**
	Salivary fistula managed medically (e.g. anticholinergic)	**II**
	Requiring drainage (not under GA). Includes radiologically guided aspiration/drainage	**IIIa**
	Requiring re-exploration and/or drainage (under GA)	**IIIb**
	Large collection obstructing airway	**IVa**

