## Progression to phase III trial

This initial study aims to inform the design, feasibility and conduct of a future phase III surgical trial. The decision to progress to this future trial will be based on variables such as recruitment rate, safety of intervention, sample size estimation and ongoing surgical equipoise. It is anticipated that further amendments to the protocol will be required to fine tune the trial design based on the outcomes of this external pilot trial and feedback from sites (both research staff and surgeons). All these issues will be discussed by the TSC once the external pilot trial has closed and a decision to progress to a phase III trial made.

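### Safety reporting is limited to Clavien-Dindo grade IV or above, so the TSC is not assured of seeing an excess of drainage, returns to theatre or treated hypersensitivity in the sealant arm during recruitment

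*Protocol article*

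**What the plan says.** Five parts of the protocol article bear on this point.

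- **Safety.** Surgical complications and sealant reactions of Clavien-Dindo grade IV or above "will be the only events reported to assess safety". Related complications "that are Clavien-Dindo grade III-b or below that meet the definition of serious are exempt from Serious Adverse Event (SAE) reporting"; they are classed as expected and "should only be recorded in the relevant section of the eCRF". All grades are nevertheless collected: because Clavien-Dindo "constitutes a primary outcome measure for the DEFeND pilot trial", "the presence of post-operative complications along with their grade will be recorded on the eCRF".
- **Data monitoring.** Interim analyses of the accumulating data are planned every 6 months. There is no independent data monitoring committee. The independent TSC members review the interim safety data and advise, on the trial's accumulated data, whether to continue; "it is anticipated that the TSC will only recommend termination on grounds of safety".
- **Table 3.** For bleeding or haematoma, drainage without general anaesthesia is grade IIIa. Grade IIIb is described as "Requiring drainage or return to theatre for haemostasis (under GA". A hypersensitivity reaction treated with medication is grade II whether mild, moderate or severe; anaphylactic shock is grade IV.
- **Blinding.** A severe hypersensitivity reaction is named as a serious adverse event.
- **Progression to phase III trial.** The decision is "based on variables such as recruitment rate, safety of intervention, sample size estimation" and continuing equipoise, and is taken after the pilot has closed.

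**The concern.** The Safety section does more than exempt expected events from expedited reporting. The exemption is a separate, later sentence. The opening sentence defines the set of events by which safety is assessed. If the interim safety data are compiled to that definition, they contain no drainage procedure, no re-exploration and no return to theatre below grade IV.

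Those are the events that a wound sealant is meant to influence. The Background lists haematoma, infection, wound breakdown and fistula as the common complications and notes that managing them may mean going back to theatre. An effect in the wrong direction would appear mainly at grade III. The only people with an independent safety role, whose only anticipated ground for recommending termination is safety, could then be working from a table that is usually empty while the informative counts stay on the eCRF.

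Hypersensitivity shows the same problem as a direct inconsistency. An event that Blinding calls serious can be grade II in Table 3. Under the Safety section it is then exempt from SAE reporting and outside the events used to assess safety.

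**Working it through.** The plan gives no figure on this point, so there is none to reproduce. The check sets the sections side by side and then illustrates the size with assumed rates.

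**1. Which events count as safety data?**

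| Event | Grade (Table 3) | Among events reported to assess safety? | Recorded on eCRF? |
|---|---|---|---|
| Severe hypersensitivity treated with medication | II | No, although Blinding calls severe hypersensitivity an SAE | Yes |
| Haematoma or seroma drained without GA | IIIa | No | Yes |
| Drainage, re-exploration or return to theatre under GA | IIIb | No | Yes |
| Anaphylactic shock, air embolism, airway-obstructing haematoma | IV | Yes | Yes |

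Data monitoring speaks of interim safety data in one sentence and of the accumulating or accumulated trial data in others. The first, taken with the Safety section, means grade IV or above. The second could include every grade. Nothing in the article says which of these the interim report follows, or whether it is split by arm.

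**2. How many sealant patients at each time?** The full sample is 25 per arm (Sample size). At about 4 patients a month (Objectives), 6 months of a 12-month recruitment period (Trial status) gives 4 × 6 = 24 randomised, or about 12 per arm. This is the review at which advice could still affect recruitment.

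**3. How often would a grade IV+ table be empty for the sealant arm?** The documents give no rate by grade, so a true risk p of 1% to 2% is assumed. P(no event) = (1 − p)^n.

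- n = 25: 0.99^25 = 0.78 and 0.98^25 = 0.60. Expected events are 25 × 0.01 = 0.25 and 25 × 0.02 = 0.5.
- n = 12: 0.99^12 = 0.89 and 0.98^12 = 0.78. Expected events are 0.12 and 0.24.
- At an assumed 5% with n = 25, the chance of at least one event is 0.72, so the result depends on the assumed rate.

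**4. What would a grade III table add?** True grade III risks are assumed in each arm. The quantity is the probability that the sealant count X exceeds the control count Y by 3 or more, that is, the sum of P(X = x)·P(Y = y) over all x − y ≥ 3 for independent binomials.

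| Assumed risk, control v sealant | 12 per arm | 25 per arm |
|---|---|---|
| 5% v 20% | 0.32 | 0.71 |
| 10% v 30% | 0.48 | 0.82 |
| 10% v 10% (no difference) | 0.04 | 0.12 |

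A grade III table is therefore more informative than a grade IV+ table. At a mid-point review it would still show no excess of this size in more than half of trials, even under these large assumed differences.

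**The case against.** The strongest reply is that the sentence opens a section about event reporting: SAE exemption, expectedness, SUSAR timelines, the SAE form and causality. Exempting expected events that are also trial outcomes is ordinary practice and does not remove them from aggregate review. Every grade is on the eCRF, interim analyses of the accumulating data are planned, and the TSC is asked to advise on that accumulated data. The detailed content of an interim report also commonly sits in the full protocol or a committee charter, neither of which is shown.

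Much of this stands. A reader might infer that the TSC would not see returns to theatre at all. The documents do not support that: no section withholds grades I–III from the independent members, and two phrases in Data monitoring are wide enough to include them.

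A reader might also infer that the progression decision rests only on grade IV+ events. That is not supported either. The decision follows closure, when all grades are available and informal differences in rates between arms are planned. The list of progression variables is open, and the safety item in it is not defined by grade.

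It is also fair that several severe sealant risks are captured, since anaphylactic shock and air embolism are grade IV. The illustrative rates are assumptions, and the systematic review cited in the Introduction suggests, without statistical significance, that sealant may protect against complications.

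The reply does not remove the stated restriction. The article does not merely leave the interim table unspecified; it says which events are reported to assess safety, and that definition does not fit the monitoring role described alongside it. The hypersensitivity conflict is likewise in the text, not an omission. The statement in Outcomes that safety will not be formally assessed across arms is no obstacle, because a descriptive table for independent members is not a formal comparison.

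**Conclusion.** The point holds as an inconsistency about what the independent TSC members review. Taken literally, the Safety section leaves drainage, returns to theatre and medically treated severe hypersensitivity out of the safety data, while Data monitoring makes safety the only anticipated ground for termination. The TSC is thus not assured of seeing an excess of these events in the sealant arm during recruitment. Whether it would in fact see them cannot be settled from the article.

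The size can only be illustrated. If the grade IV+ risk were 1–2%, a literal safety table would hold no sealant-arm event with probability 78–60% at full recruitment and 89–78% at the mid-point. The gain from adding grade III is real but modest at the mid-point. These figures rest on assumed risks, on the planned accrual of about 4 a month, and on equal allocation.

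**What to change.** Reconcile Safety, Data monitoring, Blinding and Table 3.

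1. State that the scope of SAE and SUSAR reporting is separate from aggregate safety review, and reword the opening sentence of Safety so that the grade IV threshold applies only to the former.
2. State that each 6-monthly report to the independent TSC members tabulates complications descriptively by Clavien-Dindo grade and arm, together with events attributed to the sealant, in a closed report that keeps other staff blinded.
3. Resolve the different treatment of severe hypersensitivity in Blinding, Safety and Table 3. Which classification is right is for the trial team to decide.

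The cost is a wording change and one descriptive table per report from data already on the eCRF. It needs no new data collection, no new committee and no formal comparison, and it changes no stopping or clinical rule. The table should be presented as descriptive: at about 12 per arm, the absence of a visible excess is weak reassurance.
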